### Participants

Participating schools (*N* = 42) will be recruited into three cohorts (*n* = 14 schools p/cohort) from districts located in Washington state using a stratified recruitment approach. Schools will be compensated $400 total to support time for recruitment, retention, and other research activities. Inclusion criteria for districts are: 1) presence of a district-wide commitment to implement PBIS in elementary schools, as evidenced by either having completed a PBIS training in the past two years from certified coaches or a willingness to complete the training at the outset of study participation; 2) data sharing agreements with the project investigative team (including sharing of administrative data regarding students); 3) commitment to help recruit 10 educators per elementary school to complete study assessments (*N* = 420); and 4) no previous HELM exposure. Principals and leadership teams will participate in HELM for schools assigned to that condition. The research team will invite all educators from the school to participate in surveys and PBIS trainings and contacted by email or phone to complete informed consent. We will gather de-identified school administrative data for students in each classroom with no identifiable information and, therefore, active parental permission is not needed.

*Randomization*. Random assignment will occur at the school building level because both HELM and PBIS are building-level processes. The study methodologist will generate the randomization sequence, with allocation concealed from all other study personnel and participants. We will randomize schools within cohorts with equal probability (1:1) to: 1) PBIS + HELM; or 2) standard PBIS training and technical assistance. We will use covariate constrained randomization that accounts for degree of prior PBIS implementation and school size [45, 46]. Covariate constrained randomization enumerates a large number of possible assignments of the interventions to schools and quantifies the balance across arms with regard to a set of prespecified covariates (i.e. degree of prior PBIS implementation and school size). From a subset of possible assignments that achieve adequate balance, one is randomly chosen as the final allocation of interventions for the study.

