**Fig. 2 Fig2:**
[figure not shown]
HELM mediational model: RQ2a

*Data Analytic Approach*. We will explore for baseline equivalence between conditions on all school, teacher, and student variables following Institute of Educational Sciences guidelines, with effect sizes between 0.05 and 0.25 indicating that statistical adjustment for nonequivalent baseline characteristics is required [73]. Non-equivalent baseline characteristics will be included as covariates at the school, educator, or student level, as appropriate. Following best practice guidelines, variables used for covariate constrained randomization will be included as covariates in all models [46, 74]. Data missing at random will be modeled using full information maximum likelihood estimation in mixed effects modeling or multiple imputation for other analyses. Although all analyses will use an intent-to-treat approach, we will examine the robustness of condition assignment through descriptive analyses of scores on the HELM fidelity tools. Schools that achieve 80% or higher of the maximum possible score on all HELM fidelity criteria will be considered having received a full dose of HELM training and coaching.

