All analyses will use an intent-to-treat approach in which units are analyzed based on condition assignment regardless of HELM implementation success [75]. Because the trial includes outcomes at multiple levels, the specific analytic approach will vary depending on the outcome. However, in general, analyses will employ 2- or 3-level mixed effects models reflecting data collection time points nested within educator/classroom nested within schools. We will test for significantly large ICCs at the district levels to determine if statistical nesting is necessary. Standard model-building procedures will be used [76, 77], including fitting a null model to facilitate calculation of variance accounted for in later models, fitting unconditional growth models (e.g., linear, quadratic, piecewise) to determine the optimal functional form for time, and finally, fitting models that include the variable for condition (and the condition by time interaction, as appropriate) along with covariates. Iterative models with possible covariates will be tested. Covariates not significantly contributing to the model at *p* < 0.10 based on likelihood ratio tests will be removed. We will obtain estimates of whether there were statistically significant differences between conditions on rate of change over time (i.e., slope), and whether there are statistically significant condition differences in average score on each outcome at T2 and T3. Models will be generalized, with appropriate link functions (e.g., log-link, Poisson) applied based on distributional form (e.g., dichotomous, zero-inflation). Estimations will be fit using full maximum likelihood. Models will be assessed for possible violations of assumptions. Inference will be evaluated relative to *p* < 0.05. For hypotheses/research questions with multiple DVs, we will adjust for familywise error using Benjamini and Hochberg’s False Discovery Rate [78].

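### Covariates are dropped on outcome-based p-values with no stated exemption, which is not reconciled with the covariates the article requires and can inflate the error of school-level T2/T3 contrasts

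*Protocol article*

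**What the plan says.** All but one of the relevant statements stand under Data analysis, in the Data Analytic Approach text of the Protocol article.

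- **Randomisation variables:** "variables used for covariate constrained randomization will be included as covariates in all models". The Participants section gives two of them, through "covariate constrained randomization that accounts for degree of prior PBIS implementation and school size".
- **Baseline differences:** all school, teacher and student variables are screened, with "effect sizes between 0.05 and 0.25 indicating that statistical adjustment for nonequivalent baseline characteristics is required". Then: "Non-equivalent baseline characteristics will be included as covariates at the school, educator, or student level, as appropriate".
- **Removal:** the following paragraph has "Iterative models with possible covariates will be tested. Covariates not significantly contributing to the model at" a threshold of p < 0.10 are taken out, the criterion being a likelihood ratio test.
- **Tests of condition:** the slope difference, and differences in average score at T2 and T3. "Inference will be evaluated relative to" p < 0.05, and "Estimations will be fit using full maximum likelihood".

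The article does not say how the removal rule relates to the first two rules, and it gives no count of candidate covariates.

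**The concern.** There are two problems.

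The first is wording. Two kinds of covariate are promised a place in the models, and a later sentence removes covariates by p-value without excluding either kind. Two analysts following the text could fit different models to the same outcome.

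The second is statistical and remains however the wording is read. The removal test uses the outcome. Covariates that happen to fit the 42 school values are kept and the rest are discarded. The condition test then treats the surviving model as if it had been chosen in advance. The residual variance comes out too small, because the search that produced the fit is not charged for. The contrasts exposed are the average-score differences at T2 and T3 on outcomes that vary by school, including school-level PBIS fidelity on the Tiered Fidelity Inventory (TFI), which the Measures section names as the primary outcome. The covariate set could also differ from outcome to outcome for reasons unrelated to the design.

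**Working it through.** **1. Check of the design inputs against the article's own figure.** The Power Analysis text gives minimum detectable effects of 0.23 to 0.65, 42 schools, 10-12 educators or classrooms per school, ICCs of 0.1 to 0.35, and half of post-test variance explained by pretest. Power of 80% and a two-sided 5% test are assumed here.

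- School level, one post-test: 2.8016 × sqrt(0.5 × 4/J). For J = 40 this is 2.8016 × 0.2236 = 0.626, or 0.644 with a t reference. For J = 42 it is 0.611, or 0.627 with t. These lie close to the upper end, 0.65.
- Educator level, mean of two follow-ups: the pre-post correlation is sqrt(0.5) = 0.707, so the variance factor is (1 + 0.707)/2 − 0.5 = 0.354. With 42 schools, 10 educators and ICC 0.1, sqrt(0.354 × 4/42 × (0.1 + 0.9/10)) = 0.080. The effect is 0.224, or 0.230 with t. This matches the lower end.

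The upper end of the range therefore fits a test whose effective sample is the schools, and that is the setting simulated below.

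**2. Type I error after selection.** The set-up was:

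- no HELM effect; 42 schools in 3 cohorts of 14, allocated 1:1;
- constrained randomisation on two covariates (best 10% of 100 candidate allocations);
- backward removal by likelihood ratio test at 0.10, then a two-sided 5% t test of condition;
- 12,000 trials per scenario (Monte Carlo standard error about 0.2 points, 0.3 at the highest rates).

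The number and strength of the candidates are assumptions: R² of 0, 0.2 or 0.5 for the randomisation covariates, and 0 or 0.2 for the others.

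| Further candidates | Removal applies to all | Randomisation covariates kept, others selected | All kept, no removal |
|---|---|---|---|
| 0 | 4.9-5.6% | no selection | 4.8-5.4% |
| 1 | 5.0-5.4% | 5.0-5.1% | 4.9-5.0% |
| 3 | 5.5-6.4% | 5.3-6.2% | 4.7-5.2% |
| 6 | 6.6-7.8% | 6.3-7.6% | 4.8-5.1% |
| 10 | 8.8-9.6% | 8.5-9.6% | 4.9-5.3% |

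The second and third columns differ by at most 0.3 points. So the inflation comes from selecting among the further covariates. Losing the randomisation covariates does not cause it.

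**3. How many candidates might there be?** Besides school size and the TFI, Table 1 lists 14 baseline variables: racial/ethnic composition, free/reduced lunch, implementation leadership, implementation climate, burnout, citizenship behaviour, coordination, change fatigue, three classroom behaviour ratings, test scores, attendance and discipline. With 21 schools per arm, the standard error of a standardised school-level difference is sqrt(4/42) = 0.31. By chance alone such a difference exceeds 0.05 with probability P(|Z| > 0.05/0.31) ≈ 0.87, and 14 × 0.87 ≈ 12.

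Simulating that screen followed by the removal rule (3,000 trials per scenario, standard error about 0.5 points; baseline TFI R² 0.5, school size r = 0.2, all variables averaged to school level) gave 9.3-11.2%. Keeping the screened covariates without removal gave 4.5-5.5%. With the randomisation covariates forced in and the rest still selected, the error was 9.3-10.5%.

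**4. Slope test.** In the runs of step 2 the condition-by-time test rejected in 4.4-5.3% of trials in every scenario. In a balanced random-intercept model that contrast uses only within-unit change, and main effects of covariates that are constant over time cancel out of it.

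**5. Reference distribution.** With a maximum likelihood Wald z test in place of the t test, the error was already 6.5-7.5% with the two randomisation covariates and no selection. With 10 further candidates it was 11.2-15.1% after selection and 12.1-12.4% with all of them kept. Part of any inflation under that test is therefore a small-sample matter and not due to the removal rule.

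**The case against.** The strongest defence is that the specific rule governs the general one. The randomisation variables belong in all models, and the removal sentence follows a mention of possible covariates, which most naturally means optional ones. For the two randomisation variables this reading is reasonable, so a flat contradiction, which a reader might infer, is not established. The reading does not settle the baseline characteristics whose adjustment is required. They are known only after screening and could well be counted among the possible covariates.

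A second defence is that the candidate count is unknown. Among the school demographics in Table 1, only two go beyond the randomisation covariates, and with so few the error stays close to 5-6%. The baseline screen admits only non-equivalent variables, each at its own level. This stands: the 12-14 figure requires the screen to be applied from 0.05 to every listed variable at school level, and the article does not say that it will be.

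A third is that the Abstract frames the main comparison as steeper gains over time, and the slope test is unharmed in the simple model. This also stands. It does not cover the T2 and T3 average-score comparisons, which the Data analysis section lists as well.

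Finally, an analysis plan that is not shown may name the covariates. The point does not rest on something left out, however. The article states a removal rule, and the rule is a poor one for testing condition.

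**Conclusion.** The point holds with limits. The article states an outcome-driven removal rule without exemption and does not reconcile it with the covariates it elsewhere requires. For school-level average-score contrasts the rule can raise the type I error from about 5% to roughly 6-8% with 6 further candidates, 8-10% with 10 and about 9-11% with 12-14. With three or fewer it has little effect. These figures assume 42 schools, a t reference and the covariate strengths given above.

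Three stronger inferences are not supported:

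- No single inflated error rate, such as 7-9%, follows from the plan, because it depends on a candidate count that the article does not give.
- Dropping the randomisation covariates is not what inflates the error. With only those two in play the t test stays near 5%, and in a smaller run (3,000 trials per scenario) omitting prognostic, balanced covariates altogether made the unadjusted test conservative (0.8-3.3%). Losing them would be a departure from the article's own rule, which is a separate matter.
- The slope test is not shown to be affected. That finding is limited to a balanced random-intercept model with covariate main effects only.

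**What to change.** Delete the p < 0.10 removal rule for every model that tests condition. For each outcome, fix one covariate set before outcome data are seen: the two randomisation covariates plus named baseline variables, retained whatever their p-values. If the baseline-equivalence screen is kept, it uses baseline data only, so its result can be frozen before T2 data are available. Show models with other covariates only as sensitivity analyses.

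Exempting the randomisation covariates alone is not enough, since the error was almost unchanged when only they were protected. The named set should be short, because a long fixed list also raises the error if a Wald z reference is used.

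The cost is a few degrees of freedom and less analyst freedom. The change is to wording only, and the Discussion reports that no participants had been enrolled as of February 2025.

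### Hypothesis 1a (PBIS fidelity) gets three unranked, uncorrected tests at 0.05; if any one counts as support, the false-positive rate is roughly 9–13%, not 5%

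*Protocol article*

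**What the plan says.** Under Data analysis, Data Analytic Approach, the article plans two kinds of significance statement for each outcome. The first concerns "statistically significant differences between conditions on rate of change over time (i.e., slope"). The second is "whether there are statistically significant condition differences in average score on each outcome at T2 and T3". That makes three tests per outcome: slope, T2 and T3. The threshold is the same for all: "Inference will be evaluated relative to *p* < 0.05".

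The shape of the time trend is not fixed beforehand. The plan is "fitting unconditional growth models (e.g., linear, quadratic, piecewise) to determine the optimal functional form for time", after which condition and, as appropriate, its interaction with time are added.

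The only multiplicity rule is: "For hypotheses/research questions with multiple DVs, we will adjust for familywise error using Benjamini and Hochberg" (the False Discovery Rate method).

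Three other places bear on the point:

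- Aim 1 gives Hypothesis 1a one outcome, PBIS fidelity. Hypothesis 1b has two (implementation leadership and climate). Hypothesis 1c covers the student outcomes.
- The Fidelity paragraph under Measures calls fidelity the primary outcome. The Abstract gives that label to implementation leadership.
- The Abstract describes the test as a condition-by-time interaction showing a faster rise under HELM, whereas Hypothesis 1a is worded as a difference in level.

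**The concern.** A correction rule that applies only across dependent variables does nothing for a hypothesis that has one. Hypothesis 1a is such a hypothesis, and its outcome is the one that Measures calls primary. Its three tests are correlated but not identical, so allowing any of them to carry the claim gives more than a 5% chance of a false claim. Nothing in the article ranks them, and its own wording points two ways: the Abstract towards slope, Hypothesis 1a towards level.

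The open time form makes the slope test itself indefinite. With three waves, a quadratic or a two-piece linear form reproduces the three means of each arm exactly. A quadratic has a slope that changes with time, and a piecewise form has two slopes. Until the form is known, neither the meaning nor the number of slope tests is settled.

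For hypotheses with several outcomes the stated aim is familywise control, but the named procedure controls a different quantity.

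**Working it through.** **Inputs.** Alpha 0.05 per test (Data Analytic Approach; two-sided assumed, since sidedness is not stated). 42 schools, one of them extra in each condition, so 40 without the spares (Power Analysis). 1:1 allocation (Randomization). Waves at 0, 8–9 and 12 months (Measures). Pretest explains 50% of posttest variance (Power Analysis), so r = √0.50 = 0.707.

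**Step 1: the plan's own figure.** The article states no familywise error rate. Its nearest figure is the upper end of the detectable-effect range, 0.65, taken here as the school-level case. For a baseline-adjusted comparison of J schools, SE = √(4(1 − R²)/J). With J = 40 and R² = 0.5, SE = √(2/40) = 0.2236. At 80% power (assumed, not stated) and two-sided 0.05, the noncentral t gives 0.643; J = 42 gives 0.627. So 0.65 is reproduced to within about 1% at 40 schools, as one test at 0.05 with no allowance for three. The lower end, 0.23, was not reproduced (0.26–0.28 at ICC 0.1 with 10–12 educators). It depends on settings not given and does not bear on this point.

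**Step 2: correlations among the three tests.** Each test is a contrast vector applied to the arm differences at T1, T2 and T3, whose correlation matrix is R. For contrasts a and b, the correlation is aRb′/√(aRa′ · bRb′). With times 0, 8.5 and 12 (mean 6.83):

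- slope: (−6.83, 1.67, 5.17)
- baseline-adjusted T2: (−r, 1, 0)
- baseline-adjusted T3: (−r, 0, 1)

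With a common correlation r = 0.707, T2 and T3 correlate r/(1 + r) = 0.707/1.707 = 0.41, slope and T2 0.57, and slope and T3 0.88.

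**Step 3: chance under no effect that at least one |z| exceeds 1.96** (2,000,000 multivariate normal draws per setting).

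| Tests | Assumption | Any significant |
|---|---|---|
| Slope + baseline-adjusted T2, T3 | common r = 0.707 | 11.0% |
| Same | common r = 0.5 to 0.8 | 11.8% to 10.6% |
| Same | serial correlation | 9.0% |
| Slope + unadjusted T2, T3 | common r = 0.707 | 12.7% |
| Same | serial correlation | 11.2% |
| Slope + T2, T3 implied by a linear model | common r = 0.707 | 10.3–10.4% |
| Slope + change from baseline at T2, T3 | common r = 0.707 | 9.5% |
| Two piecewise slopes + unadjusted T2, T3 | common r = 0.707 | 15.6% |

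A simulation with 42 schools and t-tests (200,000 runs, unadjusted T2 and T3) gave 12.8%, with each single test at 5.0–5.1%. Three independent tests would give 1 − 0.95³ = 14.3%.

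**Step 4: Benjamini-Hochberg as familywise control.**

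- *Two tests (Hypothesis 1b).* Both are rejected if the larger p ≤ 0.05; otherwise the smaller is rejected if ≤ 0.025. These are Hochberg's thresholds, so familywise error stays at 5%.
- *Three tests, one with a large real effect.* The thresholds are 0.0167, 0.0333 and 0.05, and the real effect takes the first rank. A true null is then rejected if the smaller of the other two p-values is ≤ 0.0333, or if both are ≤ 0.05. For independent tests this is 1 − (1 − 0.0333)² + 0.0167² = 0.0656 + 0.0003 = 6.6%.
- *Six tests, three with large real effects.* Simulation gives 9.7%. Table 1 lists at least six student outcomes: three classroom ratings, test scores, attendance and disciplinary incidents.

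**The case against.** The strongest reply is that the Abstract already points to the condition-by-time interaction, with the T2 and T3 differences there only to show when the arms diverge. The deciding contrast would then be known, and its detail is commonly left to an analysis plan that is not shown. Part of this stands: the Abstract does lean towards slope. But Hypothesis 1a is worded as a level difference, and the Data Analytic Approach gives all three tests the same threshold without ranking them. The gap also arises from what the article states, namely a correction rule whose scope passes over Hypothesis 1a, and not from silence.

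Four stronger readings are tempting and are not supported:

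- A reader might infer that Hypothesis 1a simply has an 11% error rate. That holds only if any one of the three significant results counts as support. No passage states this rule, and the figure moves with the correlation pattern and the model.
- A reader might infer that choosing the time form from the data adds further inflation. The growth models used for that choice are unconditional: they leave out condition. The choice therefore adds little error itself. What it leaves open is what slope means and how many slope tests there are.
- A reader might infer that the false discovery rate method fails for every multi-outcome hypothesis. For the two outcomes of Hypothesis 1b it coincides with Hochberg's procedure and does hold familywise error.
- A reader might take Hypothesis 1a as undisputedly the main one. Measures supports that, but the Abstract names leadership as primary, which falls under Hypothesis 1b. There the correction applies across outcomes, although the article does not say whether it also covers the three contrasts within each outcome.

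**Conclusion.** The point holds in a limited form and should be corrected. As written, Hypothesis 1a has three tests at 0.05, none ranked and none corrected. If any one counts as support, the false-positive rate is roughly 9–13%, and about 16% if a piecewise form brings a second slope test. If one contrast is named in advance, it is 5%. These figures assume two-sided tests, the plan's 50% of variance explained (or the range shown around it) and valid single tests.

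The familywise label is a separate and smaller error. It is harmless for Hypothesis 1b. For a hypothesis with three to six tests and some real effects, familywise error is about 7–10%, assuming independent tests and large real effects.

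**What to change.** 1. Fix the coding of time in advance for the confirmatory models, for example as a three-level category.
2. Name one deciding contrast per outcome at 0.05. The baseline-adjusted T3 difference is one option; a defined condition-by-time contrast, closer to the Abstract, is another. Any single prespecified contrast restores 5%. Report the others as supportive, with confidence intervals.
3. Alternatively, keep all three as decisive and extend the correction to them. Bonferroni at 0.05/3 = 0.0167 each gives 4.5% in the 42-school simulation at r = 0.707, at some cost in power.
4. For Hypothesis 1c and any other hypothesis with three or more tests, either say that the false discovery rate is controlled, or use Holm or Hochberg if familywise control is intended.
5. Reconcile the Abstract and Measures on which outcome is primary, so that it is clear which hypothesis the deciding contrast serves.

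The cost is wording in the analysis plan, and the Discussion reports no enrolment as of February 2025. The small downside is that a result significant only on a non-deciding contrast becomes supportive.
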